#### Staff outcomes

Staff outcomes will be collected at the TIC training (baseline), and again at 3-, 6-, 12- and 18-months post-training. At each time point, the 59-item Knowledge, Principal Support, Self-efficacy, and Beliefs that Predict Commitment to Trauma-informed Care Survey (73) will be used to measure commitment to TIC (6 items), support for TIC (6 items), self-efficacy to implement TIC (7 items), beliefs about trauma in the workplace (10 items), and foundational knowledge about trauma (30 items). Staff perceptions of the five TIC values within an organization are also measured using the 10-item Trauma-Informed Climate Scale-10 (TICS-10) (74). Workplace satisfaction, burnout, and fatigue are assessed using the 30-item Professional Quality of Life Scale (V5, ProQOL) (75). An Organizational Self-Assessment of TIC (76) will also be measured at each time point to assess the extent to which the organization is implementing and progressing with a TIC model in three domains: organizational readiness for trauma-informed care change (6 items), competent trauma-informed organizational, clinical, and milieu practices (11 items), and consumer and family engagement (8 items). We will also measure staff turnover rates, and supervision attendance.

#### Service-level outcomes

Outcomes at the service-level will be evaluated to determine the feasibility of and adherence to the model throughout the trial (approximately 24 months). Specifically, we will examine number and percentage of clients completing the 6-week cycle, admission and readmission rates, number of discharges and reason for discharge, average length of stay, number of individual sessions received while in treatment, time taken to receive first session, group session attendance rates, and percentage of group sessions run as per program.

#### Fidelity

Fidelity of the model will be assessed via multiple methods. The fidelity of the group program will be assessed via completion of group attendance lists, and by session checklists completed by treatment facilitators for group sessions run during a 6-week cycle of the model. Additionally, during this time, session checklists will be completed by independent observers, and inter-rater reliability checks will be conducted. To assess the fidelity of the individual CPT component of the model, clinicians will audio record sessions. A random sample (20%) of session recordings will be independently rated for treatment fidelity to ensure the core features of the relevant CPT session are delivered.

## Ethics, adverse events, and risk management processes

The study has received Human research ethics approvals by the University of Queensland (Approval number: 2020000949) and has been approved by the treatment service and the broader service organization. All participants will have substance use problems, with likely SUDs and other mental health comorbidities. Increased vulnerability and decreased social engagement must be considered, however the project has been specifically designed to support complex and typically underserved populations. As the project will be held within a residential setting, clients will have 24-h access to support, and are connected with a community worker upon leaving the program. Any safety or urgent treatment issues will be managed as per usual safety and risk management procedures of the residential treatment facility. These processes include assessing for suicide and self-harm risk on entry, development of risk management/safety plan with caseworker, and ongoing monitoring of risk. If clients do present at imminent risk of harm or other adverse events, caseworkers will work with the clients, utilizing the client’s personalized risk management plans, including hospitalization if required. Clients learn distress tolerance skills for managing difficult emotions as part of this as part of the 6-week TIC program. Further, all therapists will be trained clinicians, experienced in managing risk, distress, and discomfort in clients.

Client’s suicide risk will be assessed at follow-ups via the Outcome Measures. If participants report suicide ideation in the past 2 weeks at 1- or 3-month timepoints, the LLW case-manager for the client will instantly be informed through a client-management system, will conduct a risk assessment, and provide the client with counseling and community support services as required. For clients who are no longer active with Lives Lived Well, the risk assessment and subsequent required supports (such as connecting to community services) will be conducted by a psychologist from the research team.

Staff will be able to report adverse effects and subsequently provided with support via weekly supervision and as needed by their team leader.

The project research team meet regularly with team leaders and area managers of the service involved in the project, as well as meet monthly with organization management. At these meetings, feedback is invited on the conduct of the research and research progress is provided to the organization, as well as soliciting incidents of adverse effects. Additionally, spontaneous participant or clinician reports of adverse effects will be recorded. The model and research will be adapted in response to feedback, if required.

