#### Trauma-informed therapy

Clients with a positive screen on the PC-PTSD are assessed for symptoms of PTSD on the PCL-5 (65) with those with elevated symptoms (a score of 27+) then considered for eligibility to receive Cognitive Processing Therapy (CPT). Exclusions for the CPT component are: (a) non-fluent in English, (b) acutely suicidal, (c) a current diagnosis of schizophrenia, (d) currently experiencing a manic episode, (e) an intellectual disability that does not allow for the comprehension of the CPT material, and (f) experienced an index early childhood trauma that occurred before the age of three. Eligible clients will be offered 10 × 90 min sessions of CPT (66) delivered in-person or via telehealth/videoconference while they are in residential treatment. Clients who are discharged from the service will be offered CPT via telehealth if they have completed at least 2 sessions. The 10 sessions of CPT will be delivered twice a week over 5 weeks, to fit with the 6-week residential program [Table 2; (44)].

**Table 2 tab2:** An overview of the 10-session CPT content.

Week	Session	Content overview
Week 1	N/A	Routine screening and consenting
Week 2	Session 1	Introduction to CPT, psychoeducation, CPT overview
	Session 2	Introducing thoughts, feelings, and identifying stuck points
Week 3	Session 3	Processing events, thoughts, and feelings
	Session 4	Level of responsibility and introducing challenging questions
Week 4	Session 5	Processing challenging questions and introducing patterns of problematic thinking
	Session 6	Processing patterns of problematic thinking and introducing challenging beliefs
Week 5	Session 7	Reviewing challenging beliefs, introducing safety and trust issues
	Session 8	Processing safety and trust issues and introducing power and control issues, and esteem issues
Week 6	Session 9	Processing power and control issues and esteem issues, introducing intimacy issues
	Session 10	Processing intimacy issues, identifying future care pathways, and identifying unprocessed stuck points

Sessions were approximately 90 min long to ensure coverage of content and were scheduled with at least 3 days apart, to allow for practice between sessions. Each session was accompanied with home practice tasks where clients are asked to complete activities that map onto the concepts taught from the corresponding therapy sessions. The PCL-5 was collected at the beginning of every session to monitor symptom changes.

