## Procedure

The TIC model was developed over a 6-month period during 2020, and the initial implementation, including workforce training, occurred post development of the program. All clients will receive the residential TIC model as part of routine care. The evaluation phase of the TIC model will occur over a 12-month period once the initial implementation has been completed. Client outcomes will be assessed at baseline and 1-, 3-, 6- and 12-months follow up (till December 2022). Within 1 week of entry to the service, clients will receive verbal and written information of the trial by a research assistant and informed consent will be obtained. Only the data of clients who consent to participate in the project will be used to evaluate the effectiveness of the new model. All client participants will be followed up for intent-to-treat purposes, regardless of treatment completion. Reminders to complete the survey will be sent to participants via SMS and email. At 1-month and 3-month timepoints, the online survey and reminders will be sent as part of the service’s usual Outcome Measures procedure. At 6- and 12-months, research assistants will send out the surveys (as these time-points are not part of the services usual outcome measure procedures). Participants will be followed-up over the phone by research assistants not involved in treatment delivery or model design, if the survey is not completed within 1 week. Participants will be reimbursed $20 for completing each survey.

Staff outcomes will be collected at the TIC training, and again at 3-, 6-, 12- and 18-months post-training, via online surveys sent by email from research assistants not involved in treatment delivery or TIC model design. Staff will be sent reminders to complete the surveys by these research assistants and general reminders regarding the study by their team leader. Staff who are no longer working at the service will not be followed up.

The sustainability of the TIC model will be assessed for a 12-month period after the evaluation phase is complete, to determine if delivery of the TIC model is sustained once the formal evaluation ends. All clients who enter the service consent to their deidentified data being used for service evaluation purposes. During this time, the researchers will have minimal involvement in the running of the model. Service outcomes will be collected during this period (see below for outcomes).

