### Outcomes

#### Client outcomes

Client outcomes will be collected upon entry to the residential treatment service (baseline), and again at 1-, 3-, 6-, and 12-months later. See Table 3 for the list of measures, including measures that are collected as part of routine care and the additional measures completed for the evaluation. The primary outcome for the evaluation will be substance-related outcomes, assessed via the World Health Organization Alcohol, Smoking and Substance Involvement Screening Test (ASSIST) (67) and the Australian Treatment Outcomes Profile (ATOP) (68). Quality of life is assessed by the relevant items on the ATOP. PTSD upon treatment entry is measured using the Primary Care PTSD Screen for DSM-5 (64), a brief five-item measure of symptoms of PTSD over the last month. Those with a positive screen on the PC-PTSD (scored 3+), will be asked to complete the PTSD Checklist (PCL-5) (69), a 20-item measure of PTSD symptom severity, which will be the primary outcome for the CPT analyses. Secondary outcomes include measures of depression and anxiety using the Patient Health Questionnaire (PHQ-9) (70), (9-items) and the Generalized Anxiety Disorder Scale (GADS-7) (71) (7-items), respectively. Client satisfaction will be assessed via the five-item Patient Experience Questionnaire from the Improving Access to Psychological Therapies program (72). Open ended responses will also be included to collect feedback from the participants about their level of satisfaction with their treatment and to better inform treatment procedures.

**Table 3 tab3:** Study timelines and outcomes.

	Enrolment		Treatment		Follow up			
TIMEPOINT	*-t_1_*	*-t_2_*	*t1*	*t2*	6 weeks	3 months	6 months	12 months
*ENROLMENT:*								
*Staff informed consent*	X							
*Client informed consent*		X						
*Client eligibility*		X						
*INTERVENTIONS:*								
*Model development*	X							
*Staff training*		X						
*TIC trial*								
*Sustainability*					X	X	X	X
*Evaluation:*								
*Client measures*		X			X	X	X	X
Demographics		X						
WHO-assist		X				X	X	X
ATOP		X			X	X	X	X
PHQ-9^a^		X			X	X	X	X
GAD-7		X			X	X	X	X
PTSD screen*		X			X	X	X	X
PCL-5*		X			X	X	X	X
Distress tolerance scale		X			X	X	X	X
Resilience evaluation scale		X			X	X	X	X
PEQ					X	X	X	X
*Staff measures*	X				X	X	X	X

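### As described, client adverse effects reach the record only through service leaders and spontaneous reports; apart from suicide ideation, no scheduled harm question to participants is described

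*Protocol article*

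**What the plan says.** The section on ethics, adverse events and risk management names the routes. The research team meets regularly with team leaders and area managers, and monthly with organization management. These meetings serve for feedback and progress, "as well as soliciting incidents of adverse effects. Additionally, spontaneous participant or clinician reports of adverse effects will be recorded". A further sentence reads "Staff will be able to report adverse effects and subsequently provided with support via weekly supervision"; since it goes on to support for the staff member, it probably concerns effects on staff and is not counted here as a client route.

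Participants themselves are asked one scheduled safety question: "suicide risk will be assessed at follow-ups via the Outcome Measures", which the Table 3 footnote identifies as the ideation item of the PHQ-9. Other scheduled measures are repeated symptom and substance-use scales (Table 3). During Cognitive Processing Therapy (CPT), "The PCL-5 was collected at the beginning of every session to monitor symptom changes". On free text, "Open ended responses will also be included to collect feedback from the participants about their level of satisfaction with their treatment". Service-level outcomes cover the service's own admissions, readmissions and discharges.

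The Procedure section gives surveys at 1, 3, 6 and 12 months. The first two go out under the service's usual process. Research assistants send the last two because "these time-points are not part of the services usual outcome measure procedures". For anyone who has not completed a survey within a week, "Participants will be followed-up over the phone by research assistants not involved in treatment delivery or model design".

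**The concern.** For client harms, the described routes either ask someone other than the client or wait for a report to be volunteered. During the residential stay that may work tolerably well, because the service has 24-hour contact and its leaders hear of incidents. After discharge, leaders can pass on only what the service has learned. An overdose, a self-harm episode or an emergency attendance that involves no caseworker need not reach anyone who records it.

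The repeated scales can show that a client is worse. They are not described as recording discrete events of this kind.

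At stake is how an adverse-effect count could be read. A low count from these routes could mean few events or few reports, and nothing in the described method separates the two. The population is vulnerable, and CPT may continue by telehealth after discharge, away from the residential support. CPT is also delivered by study authors, so the clinicians placed to report spontaneously include members of the research team. The article's stated safeguard against bias from that dual role (online collection, or an independent research assistant by phone) is given for the outcome measures, not for adverse effects.

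**Working it through.** The plan states no figure on adverse-effect ascertainment, so there is none to reproduce. The check has two parts.

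**1. What each described source can record about a client**

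- *Meetings with leaders and management:* active, but the service is asked, not the client.
- *Spontaneous participant or clinician reports:* unsolicited.
- *PHQ-9 ideation item:* scheduled and put to the client; covers ideation only.
- *ASSIST, ATOP, PHQ-9, GAD-7, PTSD screen, PCL-5:* scheduled; described as symptom, substance-use or quality-of-life measures. Their items are not all listed in the article.
- *Open-ended items:* described as being about satisfaction with treatment.
- *Service-level outcomes:* the service's own admissions and discharges, not hospital or emergency attendance elsewhere.
- *Contact after discharge (community worker, telehealth CPT, risk assessment after reported ideation):* described as support or treatment, not as a means of recording events.

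No described source puts a scheduled question about overdose, self-harm, or hospital or emergency attendance to the client.

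**2. Time and contacts involved**

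Inputs: stay of 6 weeks (Trial design and sample selection); follow-up of 12 months from entry, taken as 52 weeks (Client outcomes); last survey in the service's usual procedure at 3 months (Procedure); 177 clients expected, with 130 retained at 3 months and 113 at each of 6 and 12 months (Sample size calculation).

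- Follow-up after a completed stay: 52 − 6 = 46 weeks; 46/52 = 0.885, or 88%. Early leavers have more, up to just under 52 weeks.
- Follow-up after the last service-run survey: 12 − 3 = 9 months; 9/12 = 75%. This marks who sends the survey. It does not mark an end of measurement, since the scales continue at 6 and 12 months.
- Completed contacts after the stay: 130 + 113 + 113 = 356, out of 3 × 177 = 531 possible; 356/531 = 67.0%.
- Of these, at 6 and 12 months: 113 + 113 = 226; 226/356 = 63.5%.
- Not reached at each of 6 and 12 months: 177 − 113 = 64; 64/177 = 36.2%.

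The 1-month survey is left out of the post-stay count because a client completing six weeks is still in residence then. The first two results describe where follow-up time lies; the last three describe how far the proposed questions would reach. None estimates missed events.

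**The case against.** The strongest reply is that this is a condensed article. Survey items and adverse-event forms usually sit in the full protocol, and the items inside ATOP, ASSIST and the experience questionnaire are not listed. That limits the point to what the article describes. It does not remove it: the article has a section on adverse events that names its routes, and Table 3, presented as the list of measures, contains no adverse-event item. A reader might infer that no such question exists anywhere in the trial; the document cannot show that.

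A reader might also infer that clients are not watched after discharge. That is not supported. Clients are linked to a community worker, CPT can continue by telehealth after at least two sessions, and reported ideation leads to a risk assessment by a case-manager or, for clients no longer active with the service, a research-team psychologist. What stands is that none of this is described as recording events.

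Nor does 88% of follow-up time mean that 88% of events are missed. The document offers no basis for any such figure.

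It is fair to say that the aims contain no safety objective, that no tolerability conclusion is planned, and that the remark on safety and tolerability in the Introduction is background about a cited study. It is also true that, without a comparator, fuller counts could not show whether the model caused harm. Both points limit the weight of the matter. They do not make a passively obtained count interpretable if it is reported.

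Finally, asking about overdose and self-harm creates disclosures that need a clinical response, and the case-manager alert is spelled out only for 1 and 3 months. This is a real cost. It is largely met because the ideation item is already asked at 6 and 12 months with risk processes attached (Table 3 footnote), but the pathway at those points should be made explicit.

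**Conclusion.** The point holds for what the article describes. Client adverse effects are captured by asking service leaders and management and by spontaneous reports; the only scheduled safety question to participants is about suicide ideation. Overdose, self-harm, and hospital or emergency attendance after the stay may be under-recorded. The size is unknown: 46 of 52 weeks shows how much follow-up the described routes cover least well, not how much is lost.

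This rests on three assumptions: that the full protocol adds no such question, that the unlisted questionnaire items do not already ask about these events, and that the expected recruitment and retention are achieved. The article contradicts nothing here, and the primary client analysis does not depend on it. It is a cheap improvement to a stated but weak method.

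**What to change.** 1. Add a short fixed set of harm questions to the existing 1-, 3-, 6- and 12-month surveys, and to the phone follow-ups, for all consenting participants: hospital or emergency attendance, overdose, self-harm, and any other harmful event since the last contact.
2. Route concerning answers through the existing case-manager or research-psychologist risk pathway at every time point, naming 6 and 12 months explicitly.
3. Report solicited events with the number answering at each time point, separately from spontaneous and service-reported events.
4. Draw no tolerability conclusion from passive reports alone. This and the separate reporting of sources remain possible even if the questions cannot be added in time.

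Cost: slightly longer surveys, an ethics amendment, some clinician time to respond to disclosures, and probably a higher recorded event count. No new contact points are needed, since the surveys are already sent and reimbursed. The roughly 36% not reached at each of 6 and 12 months would still depend on the existing routes.

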## Dissemination

The findings will be disseminated to treatment services and through conferences and publications in scientific journals. Data will be collected and stored electronically in a secure data file, only accessible by the research team. De-identified research data may be used as comparative data in future projects for secondary analysis with the consent of participants.

## Conclusion, strengths, and limitations

This study details a model of trauma-informed care for residential substance use treatment that was co-developed with key stakeholders. The new model includes workforce development, ongoing supervision for staff, the inclusion of trauma screening and feedback, psychoeducation and coping strategies; integrated trauma-informed care into a 6-week group program, and the provision of specialist trauma-focused therapy. We will examine client, staff, and service outcomes over 12 months post implementation; and the sustainability of the delivery of the model will also be examined. Strengths of the current study include this holistic and codesigned approach, the use of validated measures across individual (micro), staff (meso), and organization (macro) levels, and examining outcomes over a 12-month period. The use of a single-arm uncontrolled design conducted at one site means no conclusions can be made about the comparative benefits of trauma-informed care over usual treatment and the generalizability of the model to other service settings. Further, research team was involved in the development of the model and the delivery of aspects of the model, and also subsequently will be involved in the collection of outcome measures and analysis. This design can affect the objectivity of data collection and analysis. Participants may alter their behavior or responses, consciously or unconsciously, based on their awareness of the researchers’ role and expectations, leading to response bias. Additionally, researchers may unintentionally interpret or analyze data in a manner that aligns with their preconceived notions or desired outcomes, introducing confirmation bias. To mitigate these risks, outcome measure will be collected online where possible and by an independent research assistant via phone, and we will ensure transparent reporting of methods, data handling, and potential conflicts of interest, to enhance the trial’s transparency and reproducibility.

